### The organization of the trial

The implementation of such a complex intervention program requires detailed preparation prior to the start of the trial. After randomization, a steering committee was set up to identify all the necessary steps to ensure the successful implementation of PEPITES.

A presentation to the teaching staff and the school management team was made by the scientific manager and a professional prevention trainer from the JDB Foundation before the trial started.

In each secondary school, key contact person was nominated (school nurse or Principal Education Advisor) so as to ensure coordination with the JDB Foundation team. This contact person was responsible for overseeing the overall organization of the interventions: draw up a planning, reserve the classrooms, inform the teachers and pupils concerned, distribute an information letter to the parents and collect their consent forms.

### Data collection

The procedures and tools for data collection were created by the JDB Foundation team and were tested before the implementation of the trial in various secondary schools not included in the study.

Regarding the process, qualitative methods (semi-directive interviews and completion of a log-book notifying absences, refusals, computers problem as well as comments relating to the data collection) were put in place.

Questionnaires were used to identify reasons for parents’ refusals and to collect the opinions of the main participants (teaching staff, management team).

Regarding the pupils whose parents had given their authorization and who agreed to participate, the answers to the questions were collected by means of computerized and anonymous self-assessment questionnaires (Table 2), completed in class during school time. The conditions for completion of the questionnaire were to be alone at the computer under the supervision of two adults per class to avoid any copying or minimize reporting bias and to help if necessary.

**Table 2 Tab2:** Guarantee of anonymity

The self-assessment questionnaire contains a code which allows the answers from the same pupil to be followed from year to year. This numbered code was randomly generated and assigned to each pupil in the trial. The code is recorded in a list with the pupils’ names which is held by the headmaster of the school in his role as a reliable third party: the headmaster does not have access to the pupils’ answers; the JDB Foundation team which performs the analysis does not have access to the list of pupils’ names. Each time a new questionnaire is completed the code is again supplied to the pupil thanks to the paper list held by the headmaster of the school. This information is also included in the information letter to parents and pupils before completion. The procedures put in place have met that the National Commission for Data Protection and Liberties (CNIL -France) requirements and has authorized the implementation of the PEPITES trial.	

The pupils were clearly informed that neither the teachers, nor their parents, nor anybody else could match their name to their answers. Pupils were also informed that they had the right to refuse to take part.

The questionnaires are completed at different times:for the intervention groups: T0 at the start of each school year; T1 and T2 after each educational session; T3 at the end of year 2; and T4 at the end of year 4.in the control schools, data was collected at T0, T3 and T4.

The questionnaires T0, T3 and T4 cover the various determinants which may play a role in starting smoking and in becoming a regular smoker. The same basic questions (T0) are used at each follow-up so as to provide data with comparable results, whereas other questions are included (T3 and T4) to explore questions of secondary research interest.

The questionnaires T0, T3, T4 have 2 sections:one describing some personal and socio-demographic characteristics of the pupil, his family surroundings with regard to passive smoking, his knowledge and beliefs regarding smoking, and his future intentions regarding consuming tobacco,the other describing his behavior with regard to tobacco use that is: experimenter, regular or occasional smoker, ex-smoker, non-smoker. The questions concerning smoking are those used in surveys carried out at the national level in France [18] and in Europe [19].

The questionnaires T1 and T2 evaluate the acquisition of knowledge and the modifications of behavioral determinants linked to the workshops. For the educational sessions which measure taste, the data measured by electrogustometer is not collected.

Logical checks for pertinent questions are carried out by the data entry system. .

### Statistical analysis

Data analysis will follow a pre-specified plan including:➢ The initial description of the study population and the comparison between the 3 groups. Observed differences which are linked to smoking, should lead to an adjustment when the groups are compared;➢ Follow-up of pupils over time: carrying out the planned workshops, number of ‘lost’ pupils, how well the questionnaires are filled in, modifications of the collected characteristics and behaviors;➢ Searching for factors which influence smoking;➢ Comparison of the 2 principal outcomes at the end of year 2 (2 groups) and at the end of year 4 (2 and 3 groups) and the time trends over 4 years of such outcomes. Taking into account the cluster effect, matched data, the 2 analysis of the trial and any relevant adjustment factors, (different logistical regression models adapted to the types of data will be studied).

For all these analyses, the software STATA/SE version 13 will be used.

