### Population selection and randomization

A partnership convention was signed between the JDB Foundation and the Essonne National education authority which designated 6 secondary mixed sex state schools for the PEPITES trial as part of their commitment to health education.

After this designation and before randomization, school head teachers were sent detailed information of the study protocol, followed by a visit by study team members. Then a member of the school management was designated to be the key contact for the study investigators.

The randomization process was carried out by a study investigator during a meeting organized at the JDB Foundation where representatives of each secondary school were present.

The 6 schools were allocated to 3 groups of 2 clusters each (Fig. 1):one group of 2 secondary schools with 2 educational workshops per school year; that is 8 interventions per secondary school over the 4 years,one group of 2 secondary schools with 2 educational workshops per school year; that is 8 interventions per secondary school over the 4 years, with one of the workshops dedicated to measure taste with the electrogustometer during the 3rd and 4th years,

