### Study population

In each secondary school, all pupils in year 1 (grade 6) at the time of the survey, with a signed parental authorization form (94% of year 1 pupils), have been included in the PEPITES trial.

Written parental authorization was requested for the whole duration of the trial after sending a letter which outlined the principal objectives of the trial and the intervention undertaken. The pupils could also refuse to participate even if the parents had given their authorization.

At the start of the study in September 2014, the included population was 744 pupils covering 33 classes in the 6 secondary schools and were expected to be followed, during the 4 years of secondary school.

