### Power of the study

The number of pupils that could be included in the trial is around 750 split into 3 groups of the same size: one control group (T), 2 intervention groups: (A) without EGM experimentation and (B) with EGM use in years 3 and 4. We calculated the rate of reduction of increase in the 2 principal outcomes we could detect, with a global risk α of 5%, a risk β of 20% and an intra-cluster correlation coefficient of “starters and regular smokers” at base line of 0,020 (one-sided test).Comparison Control (T) versus Interventions (A + B) at the end of year 2 on the reduction in increase of *“tobacco use initiation*” (where the increase rate in Essonne is around 10% at the end of the 2 first years of secondary school), and considering that the intervention group A + B (N1) will included ±500 pupils and the control group T (N2) ± 250 (N1/N2 = ½), a significant reduction **≥5.5%** could be detected**.**For the «regular smokers» criterion (where the percentage is estimated at 5% in Essonne at the end of year 2 and 10% in year 4), a significant reduction ≥**4%** at the end of year 2 and **≥ 6.5%** at the end of year 4 could be detected .Comparison 2 by 2 of each of the 3 groups (a control group and 2 intervention groups), for the final analysis at the end of year 4, we will be able to demonstrate a significant reduction increase **≥10%** of “starters” (from the present 25% rate) and a reduction **≥8%** of regular smokers (from the present 10% rate) .

Taking into account in the analysis the factors linked to these 2 outcomes and using appropriate multiple regression analysis and multi-level modeling should allow for an increase in power.

In order to reduce loss of power, the number of pupils lost to follow-up (final questionnaire not filled in at the end of year 2 or year 4) will be minimized by actively searching for them if absent at the time of completing the questionnaire or through the organization of catch-up educational workshops whenever possible.

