### Contamination

The possibility, for the control group, to be influenced by the intervention group is unavoidable if the random selection process is carried out on an individual basis, which leads to the pupils in the compared groups spending time and communicating with each other and possibly copying each other, which can reduce the effect of the interventions and thus the possibility of it being identified. Furthermore it would be unethical not to propose actions which aim to improve health to all the pupils of the same class.

To avoid this phenomenon, the cluster randomization design will determine at random the group allocated to each participating school. With this methodology all of the pupils from one school belong to the same group: either intervention, or control. Agreement of schools to participate occurs before randomization which can leave certain schools frustrated if designated as a control group and they may feel aggrieved; consequently they may try to compensate by involving other preventive actions, which may of course incur a major bias to the trial. It is vital that the control schools understand the importance of their “passive” participation and to propose other educational activities which do not interfere with the trial’s objective. The cluster design may also leads to an increase in the variability of the outcomes and consequently a loss of power which must be compensated for by increasing the number of subjects included in the trial.

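### Two schools per arm leave 2 to 4 degrees of freedom, so the planned logistic and multilevel models would exceed a 5% error rate if tested against a large-sample z reference

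*Protocol article*

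**What the plan says.** Under Population selection and randomization: "The 6 schools were allocated to 3 groups of 2 clusters each". The Contamination part of the Discussion confirms that the school is the randomised unit: "the cluster randomization design will determine at random the group allocated to each participating school". Under Study population, "the included population was 744 pupils covering 33 classes in the 6 secondary schools", about 124 pupils per school.

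Outcomes measures sets two kinds of principal comparison. For experimentation it is both intervention groups together against control (4 v 2 schools). For regular smoking it is the three groups two at a time (2 v 2 schools).

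Statistical analysis takes clustering, matched data and adjustment factors into account, and adds that "different logistical regression models adapted to the types of data will be studied". It names no estimator, standard error or reference distribution.

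Power of the study assumes a one-sided test, global α of 5%, β of 20% and an ICC of 0.020. It then says that accounting for factors linked to the outcomes and "using appropriate multiple regression analysis and multi-level modeling should allow for an increase in power". The Contamination section says that power lost to clustering has to be made up with more subjects.

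**The concern.** Wald tests from mixed logistic models, and tests using cluster-robust standard errors, rely on a large number of clusters. Here the variance that decides the test is estimated from six schools, or from four in a 2 by 2 comparison. With so few, the estimate is unstable and, for some estimators, also biased downwards. A z critical value ignores this.

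The article does not treat the number of schools as a limit. It looks for extra power in multilevel modelling and in more pupils, and neither adds a school-level degree of freedom. At stake is ordinary variation between schools being read as an intervention effect, in a trial whose positive result is meant to lead to transfer to other schools.

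**Working it through.** **Inputs.** Six schools, two per arm; ICC 0.020; one-sided 5%; "the intervention group A + B (N1) will included ±500 pupils and the control group T (N2) ± 250". I use 125 pupils per school (750/6). The z reference is an assumption, because the article gives none.

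**1. The article's own figure.** It states no error rate beyond α, so the nearest figure to reproduce is the detectable fall in initiation of 5.5 points from 10%. With r = 2 and pooled rate (0.10 + 2 × 0.045)/3 = 0.0633, the control-arm size is

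n = [z_α √(3 × 0.0633 × 0.9367) + z_β √(2 × 0.09 + 0.042975)]² / (2 × 0.055²).

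- One-sided 5%, no clustering: [1.645 × 0.4219 + 0.8416 × 0.4722]² / 0.00605 = 197.
- Two-sided 5%, no clustering: [1.960 × 0.4219 + 0.8416 × 0.4722]² / 0.00605 = 248, which matches the planned 250.
- One-sided with the school design effect 1 + 124 × 0.02 = 3.48: 197 × 3.48 = 686.

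The figure is therefore not reproduced from its stated inputs. That is a separate matter. It matters here only because the article offers no power figure that reflects six schools.

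**2. Degrees of freedom.** A+B v T: 6 − 2 = 4. Two by two: 4 − 2 = 2.

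**3. Tail areas.** An unbiased variance used with z rejects with probability P(t > 1.645): 8.8% on 4 df. On 2 df it is 0.5 − 1.645/(2√(2 + 1.645²)) = 12.1%. For 2 v 2 schools the cluster-robust variance with the G/(G−1) factor is two-thirds of the pooled school-level variance. The test then rejects beyond 1.645 × √(2/3) = 1.343, with probability 0.5 − 1.343/(2√(2 + 1.343²)) = 15.6%.

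**4. Null simulation.** Beta-binomial school proportions, 200,000 trials per setting, 125 pupils per school, rates of 10% and 25%, no effect, nominal one-sided 5%, ICC 0.02:

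| Test | 4 v 2 schools | 2 v 2 schools |
|---|---|---|
| Cluster-robust, z | 12–13% | 15–16% |
| ML-type Wald, z | 11.5–12% | 13.5–14% |
| REML-type variance, z | 8.5–9% | 9.5–10% |
| School-level t | 5–6% | 5% |

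The model-based variances are floored at the binomial variance, which is why they can fall below the tail areas in step 3. Fitting actual random-intercept logistic models (4,000 runs per setting) gave 11.5–12.3% and 13.9%.

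**5. Sensitivity to the ICC.** At 0.005 the model-based Wald tests fall to about 6–9%, while cluster-robust z stays at about 12–16%. At 0.05 the ML-type test gives 13–16%, and the fitted random-intercept model about 21% for 2 v 2.

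**6. Power with the error rate held at 5%.** The variance of a school proportion is p(1−p) × 3.48/125. The one-sided critical value is 2.13 on 4 df and 2.92 on 2 df. Power comes from the non-central t.

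- Initiation, 10% v 4.5%, pooled: SE = √(0.002506/2 + 0.001196/4) = 0.0394; 0.055/0.0394 = 1.40; power about 32% (34% if the two arm variances are averaged).
- Starters, 25% v 15%, 2 v 2: SE = √(0.005220/2 + 0.003550/2) = 0.0662; ratio 1.51; power 27%.
- Regular smokers, 10% v 2%, 2 v 2: SE = √(0.002506/2 + 0.000546/2) = 0.0391; ratio 2.05; power 40%.

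**7. Randomisation test.** There are C(6,2) = 15 ways to choose the control schools, and C(4,2) = 6 ways to split four schools. The smallest one-sided p is 1/15 = 0.067 or 1/6 = 0.167.

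**The case against.** The strongest reply is that these error rates belong to a test the article does not specify. It is a condensed article that refers to a pre-specified plan. Estimator, reference distribution and small-sample degrees of freedom commonly sit in that plan, so their absence here is no finding. This stands. A reader might infer that the trial will reject a true null 12–16% of the time, or that small-sample methods have been left out. The document supports neither reading.

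The inflation also varies. A REML-type variance or a low ICC brings it well below twice nominal. The 0.020 is a baseline value. Baseline and covariate adjustment could lower the residual between-school variance, and the direction by year 4 is unknown. That also stands.

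The power sentence covers adjustment for prognostic factors as well as multilevel modelling, and the former can improve precision. So deleting the whole sentence would go too far.

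What remains does not depend on the unseen plan. Six schools and the degrees of freedom are fixed here. The family of models is named, and its ordinary large-sample test has the wrong size with so few clusters. Set against a calculation that already includes the ICC, multilevel modelling brings no power. Treating classes as clusters is no escape, because schools were randomised.

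**Conclusion.** The concern holds conditionally. If the named models are tested against z at ICC 0.02, a nominal one-sided 5% becomes about 12–13% for A+B v T and 14–16% for each 2 by 2 comparison with cluster-robust or ML Wald tests. Other estimators and lower ICCs give less, as shown. A flat claim that false positives are two to three times as frequent as stated would not hold across these choices.

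The results rest on equal schools of 125, no covariate adjustment and the baseline ICC applying at follow-up. The credit given to multilevel modelling in the power section is wrong as stated. A small-sample correction restores the 5% level but not the stated 80% power.

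**What to change.** - Make the primary inference for both principal outcomes a school-level analysis: one proportion per school, adjusted for baseline at pupil level so that no school-level degrees of freedom are spent. Use t with 4 df for A+B v T and 2 df for each 2 by 2 comparison, and report risk differences with confidence intervals. The 4 df assume that A and B share one mean. The alternative is a stated three-arm school-level model with its residual 6 − 3 = 3 df.
- Keep mixed logistic models as supportive analyses, with small-sample degrees of freedom in place of z.
- Reword the power sentence so that only adjustment for prognostic factors is said possibly to improve precision.
- If a randomisation p-value is reported, call it descriptive, since it cannot reach 5%.

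No data collection changes. The cost is wider intervals and an open statement that, at ICC 0.02 and a true 5% level, power at the stated effects is about 27–40%. More pupils in the same six schools would not restore the missing degrees of freedom.

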## Discussion

Carrying out, in France, a randomized intervention trial on health prevention risks in the school environment raises a certain number of specific problems which it would seem useful to detail for other educational actors who would like to carry out a similar complex study.

This discussion concerns the acceptation, the interest and the cooperation of the National Education partners, the minimization of the risks of contamination, information given to parents and pupils and their consent, ensuring that collected data remains anonymous, representativeness of the schools that take part….

### Agreement of partner schools to participate

First of all it is necessary to convince the regional Head of the National Education (Rectorat) of the interest of the project and especially of the methodology of the study allowing an « evidence based » evaluation which is a vital element to allow a possible transferability to other schools.

The search for schools with which to collaborate relies on several key principles [20] which are: clarity of information, understanding and acceptance of the methodology by partners and parents, minimization of the work load for the school staff, a planned and reactive organization and regular contact between all parties.

The identification of a key contact person for each secondary school (often the school nurse as the subject of the trial is health) makes it easier to carry out a rigorous study. The specific context (public or private, social environment…) of each school must be taken into consideration as much as possible.

### Contamination

The possibility, for the control group, to be influenced by the intervention group is unavoidable if the random selection process is carried out on an individual basis, which leads to the pupils in the compared groups spending time and communicating with each other and possibly copying each other, which can reduce the effect of the interventions and thus the possibility of it being identified. Furthermore it would be unethical not to propose actions which aim to improve health to all the pupils of the same class.

To avoid this phenomenon, the cluster randomization design will determine at random the group allocated to each participating school. With this methodology all of the pupils from one school belong to the same group: either intervention, or control. Agreement of schools to participate occurs before randomization which can leave certain schools frustrated if designated as a control group and they may feel aggrieved; consequently they may try to compensate by involving other preventive actions, which may of course incur a major bias to the trial. It is vital that the control schools understand the importance of their “passive” participation and to propose other educational activities which do not interfere with the trial’s objective. The cluster design may also leads to an increase in the variability of the outcomes and consequently a loss of power which must be compensated for by increasing the number of subjects included in the trial.

### Consent, anonymity and data collection

As well as the agreement of the teaching staff it is also necessary to obtain the agreement of the parents and pupils.

In France, the parental written consent form is mandatory for minors (legal obligation) and to obtain it is the responsibility of the headmaster. Written information, or oral information for the parents, is compulsory. A letter summarizing the main objectives of the survey, as well as details of the interventions, has to be sent to parents at least 2 or 3 weeks before the trial began. The parents are therefore able to notify their refusal.The pupils, authorized by their parents to participate, agreed to participate by the fact they filled in the questionnaire that they are given. The pupils could refuse to participate on the first day of the trial without the need for any justification and with no penalty for their school record. However, if we want to have a participation level close to 100% and honest answers, the pupils must have understood on the one hand the objective of the trial and on the other hand the fact that the answers are anonymous. They must be reassured that it is impossible for their answers to be communicated to their parents or teachers. A clear and full explanation on this point is all the more important since the questions relate to acts which, for them, are not allowed. The message to the pupils must be friendly, confident and adapted to their age group.

Use of electronic tablets to fill in the questionnaires is greatly appreciated by the pupils and as a result constitutes a user-friendly tool which is very useful for data collection. If there are technical problems (computer breakdown, no internet connection), questionnaires in paper format should be ready to be used.

The procedures for filling in the questionnaire must be explained at the beginning of the session by the study team. The pupils are invited to ask questions throughout the session if they do not understand a question. The teachers are asked to identify the pupils who have difficulty reading or concentrating and who may need extra help to be able to participate. Once the students have completed their questionnaires, the data must be sent directly to a secure server.

